### Data Collection and Management

The clinical assessment staff will collect data on IOP (mm Hg), best corrected visual acuity (logarithm of the minimum angle of resolution), SC area (μm^2^), SC diameter (μm), TM width (μm), and TM thickness (μm), as well as responses to the Quality of Vision Questionnaire. Cases that are discontinued will be retained for subanalysis; these cases will be particularly useful for evaluating outcomes such as AEs and adherence. All participants will undergo a comprehensive ophthalmic examination at baseline and after the intervention. When participants enroll for the study, trained clinical researchers and outpatient physicians participating in the trial will enter participant information into electronic case report forms. All study data will be entered into a specialized management program and stored securely in a database to ensure confidentiality. Designated statisticians from the TMUEH research team will analyze the anonymized data according to the trial plan. Participants will be informed in advance and encouraged to actively cooperate with study procedures to minimize attrition. Although AEs are unlikely in this study, the intervention will be suspended upon detection of any ocular symptoms of concern during slit lamp examination. Treatment for the AE, along with regular telephone and SMS text message updates, will be provided to those affected. All AEs are documented and reported to the trial steering committee. Participants unable to complete subsequent follow-up will be withdrawn from the study. Those who experience intolerable side effects will receive treatment and be removed immediately from the study.

### Statistical Methods

Following the guidelines for statistical analysis plans in clinical trials [18,29], all statistical analyses will be conducted using SPSS software (version 25.0; IBM Corp). The significance level is set at 5% (2-tailed), with a 95% CI. The normality of data distribution will be assessed using the Shapiro-Wilk test. Data will be compared using 2-way repeated measures analysis of variance. If the hypothesis is unmet (*P*>.05), the Greenhouse-Geisser correction will be applied. Multiple comparisons will be made between groups at different time points using the Bonferroni-Holm correction. If the Shapiro-Wilk test indicates that the data are not normally distributed (*P*<.05), nonparametric tests will be used: paired comparisons will use the Wilcoxon signed-rank test, and between-group comparisons will use the Kruskal-Wallis H test. Statistical significance will be considered at *P*<.05 for 2-tailed tests unless otherwise specified. To ensure participant safety, the distribution of AEs will be described for both digital ocular massage and EyePeace ocular massage groups. The incidence rates of AEs were compared using the chi-square test or the Fisher exact test, as appropriate. An intention-to-treat analysis will be the primary analytic approach. All participants will be included in the analysis based on their original allocation, regardless of protocol adherence. For missing data, multiple imputation will be performed using the fully conditional specification method, assuming data are missing at random. A sensitivity analysis using a per-protocol approach will also be conducted to compare results. Given the short duration of this study, an interim analysis will not be performed.

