#### Mobile App–Based Quality of Vision Questionnaire

The original Quality of Vision Questionnaire includes 10 visual symptoms, measured in terms of frequency, severity, and impact on daily activities. It was designed to assess patients’ subjective visual experience, especially after refractive or cataract surgery [26]. In this study, participants will complete the Quality of Vision Questionnaire [26] before and after ocular massage to assess subjective visual disturbances, visual clarity, and visual discomfort. The questionnaire will be delivered via a web application on the WeChat platform (Tencent Holdings Ltd) [27]. An independent examiner will perform all measurements to minimize bias, and data will be analyzed for statistical significance using appropriate paired comparison tests. In addition to the Quality of Vision Questionnaire, 3 items will be administered to measure overall quality of vision score (Likert scale, 0-10), ocular pain score (Likert scale, 0-10), and ocular discomfort score (Likert scale, 0-10; Multimedia Appendix 1).

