### Sample Size

On the basis of the stated assumptions (a common SD of 1.9 and a maximum mean difference in IOP between groups of approximately 2 mmHg), a total of 36 participants (72 eyes [participants will contribute both eyes unless exclusion criteria apply]; 3 groups; 24 eyes per group) are required to achieve 90% power at α=.05 [1,5]. This corresponds to 3 groups of equal size in a randomized controlled trial. The calculations use a 1-way analysis of variance to test overall mean differences and consider a moderate to large effect size in IOP reduction. Allowing for a 10% dropout rate, the recruitment target is 40 participants (80 eyes). If further data refine the expected mean difference, the sample size will be adjusted accordingly (larger samples for smaller expected differences and vice versa).

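### The pairwise arm comparisons are worded as IOP at each time point, baseline included, and neither they nor the nonparametric fallback is tied to change or to baseline-adjusted IOP

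*Protocol article*

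**What the plan says.** All references are to the protocol article.

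- **Hypothesis (Objectives).** EyePeace is expected to lower IOP more, and more consistently, than digital massage. This is a claim about change in one arm against change in another.
- **Time points (Participant Timeline).** There are two: baseline and 10 minutes after the intervention.
- **Main model (Statistical Methods).** A 2-way repeated measures ANOVA. No effect in it is named as the deciding test, and no baseline covariate is mentioned.
- **Follow-up tests (Statistical Methods).** "Multiple comparisons will be made between groups at different time points using the Bonferroni-Holm correction".
- **Fallback if Shapiro-Wilk is significant (Statistical Methods).** "paired comparisons will use the Wilcoxon signed-rank test, and between-group comparisons will use the Kruskal-Wallis H test". The variable given to Kruskal-Wallis is not stated.
- **Questionnaire.** Its own section says "data will be analyzed for statistical significance using appropriate paired comparison tests".
- **Planning figures (Sample Size).** "a common SD of 1.9 and a maximum mean difference in IOP between groups of approximately 2 mmHg", with "3 groups; 24 eyes per group", which "are required to achieve 90% power at α=.05". The section does not say whether the SD is of raw IOP or of change.

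**The concern.** The question is whether IOP falls more in one arm than in another. Three features of the wording lead away from it.

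1. Three arm pairs at two time points naturally give six tests. Three of these compare pre-intervention IOP between randomised groups. They cannot inform on massage, yet they share the Holm correction with the three that can.
2. The three post-intervention tests, as worded, compare IOP levels and ignore the baseline value measured in every eye.
3. The fallback offers a within-arm test plus a between-arm test not tied to change. A within-arm test cannot separate massage from a drift common to all arms, such as from rest or repeat tonometry. Separating these is the purpose of the no-massage arm.

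At stake is precision in a small trial. There is also the risk that the pairwise answer on EyePeace versus digital massage rests on a different quantity from the omnibus test, or changes with the result of a normality pretest.

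**Working it through.** **1. The plan's own figure.** One-way ANOVA with three groups, SD 1.9, α = 0.05 and equally spaced means 0, 1, 2 mm Hg:

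- f = √(2/3)/1.9 = 0.430
- noncentrality = 72 × 0.430² = 13.3
- power at 24 per group = 0.902, and 24 is the smallest n reaching 90%

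The stated figure reproduces. It treats eyes as independent and uses no baseline information.

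**2. What the repeated measures ANOVA contains.** With two time points, the group-by-time interaction equals a one-way ANOVA of change. The group main effect instead averages in the baseline. In simulation (24 independent eyes per group, 2 mm Hg maximum difference, ρ of 0.3, 0.6 and 0.8, 2,000 runs per setting) the main effect has power of only 0.37 to 0.63. It therefore matters which effect is named.

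**3. Precision of the three candidate analyses.** Let σ be the SD of raw IOP, equal at both times, and ρ the baseline–post correlation, which the document does not give.

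- Post-only variance: σ²
- Change-score variance: 2σ²(1−ρ)
- Baseline-adjusted (ANCOVA) variance: σ²(1−ρ²)
- ANCOVA/change = (1−ρ²)/[2(1−ρ)] = (1+ρ)/2
- ANCOVA/post-only = 1−ρ²

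| ρ | ANCOVA/change | ANCOVA/post-only |
|---|---|---|
| 0.5 | 0.75 | 0.75 |
| 0.6 | 0.80 | 0.64 |
| 0.7 | 0.85 | 0.51 |
| 0.8 | 0.90 | 0.36 |

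**4. Pairwise power.** Assumptions: 12 participants per arm analysed as means of two eyes, between-eye correlation 0.8, and 1.9 as the SD of raw IOP.

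- SD of a participant mean = 1.9 × √((1+0.8)/2) = 1.9 × √0.9 = 1.802
- Noncentral t for 2 mm Hg, 22 df, α = 0.05/3. The degree of freedom spent on the covariate is ignored.

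| ρ | Post-only | Change | ANCOVA |
|---|---|---|---|
| 0.5 | 0.56 | 0.56 | 0.70 |
| 0.6 | 0.56 | 0.67 | 0.78 |
| 0.7 | 0.56 | 0.81 | 0.88 |
| 0.8 | 0.56 | 0.95 | 0.97 |

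**5. Cost of the baseline tests alone.** Post-only power at the first Holm step is 0.45 at 0.05/6 and 0.56 at 0.05/3. The first step is the strictest, so this overstates the loss. With the full Holm procedure simulated on 24 independent eyes per group, the 2 mm Hg post-intervention difference is found in about 81% of trials with six tests and about 89% with three.

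**6. If within-arm verdicts were compared.** Suppose each of three arms rejects with the same probability p. The chance that the verdicts disagree is 1−p³−(1−p)³, which cannot exceed 75% (at p = 0.5). Simulated with no true arm difference, a change SD of 1.9 and 24 independent eyes per arm:

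| Common drift (mm Hg) | Verdicts disagree |
|---|---|
| 0 | about 14% |
| 0.25 | about 24% |
| 0.5 | about 53% |
| 0.75 | about 75% |
| 1.0 | about 64% |
| 1.5 | about 14% |

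The document gives no drift figure, so only the range is informative.

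**The case against.** The strongest reply is that the plan already tests change between arms. The interaction in the named ANOVA does so, uses the baseline, and is not misled by a drift common to all arms. This stands. A reader might infer that the plan has no between-arm test of change, but the parametric route contains one. What it lacks is a statement that this test decides, and pairwise contrasts on the same quantity.

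Second, Kruskal-Wallis may be intended for change scores, and a full analysis plan may say so. This also stands: the article is silent on the point. Likewise, the article does not define the Holm family, so six tests is the natural reading and not a stated fact. Nor does it say that within-arm verdicts will be compared across arms; it lists a separate between-group test. The questionnaire sentence is weak support, because the Statistical Methods section still covers between-group comparison.

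Third, ANCOVA against a change score is a choice between two valid analyses, with a modest gain. That is fair. Setting post-only power of 45% against adjusted power of about 70–97% would overstate the case. It merges two changes (fewer tests and adjustment), takes the weakest comparator, and uses the first Holm step only.

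What remains is that the comparisons the section does specify are worded by time point, and the hypothesis is not.

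**Conclusion.** The concern holds in a limited form. The plan contains a sound omnibus test of change but does not name it as decisive. Its pairwise tests, as worded, include baseline and use unadjusted IOP, and its fallback is not tied to change. This does not invalidate the trial. It is a correctable loss of precision and clarity that should be fixed.

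Against the interaction analysis, adjustment cuts variance by 10–25% for ρ of 0.5–0.8. Against post-only comparisons the cut is 25–64% over the same range. Dropping baseline tests adds about 8 percentage points of power under full Holm with independent eyes.

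The size of these gains rests on assumed ρ and between-eye correlation, and the power figures take 1.9 as the SD of raw IOP. The direction of the adjustment gain holds for any ρ between 0 and 1. Adjustment addresses the size of the IOP reduction, not the part of the hypothesis about its consistency.

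**What to change.** - **Primary analysis:** post-intervention IOP by arm with baseline IOP as covariate, allowing for two eyes per participant.
- **Multiplicity:** Holm over the three post-intervention arm contrasts only.
- **Fallback:** if residuals are clearly non-normal, test the same between-arm quantity, by a participant-level permutation test of the adjusted contrast or Kruskal-Wallis on participant-mean change.
- **Secondary outcomes:** use the same between-arm approach for Schlemm canal, trabecular meshwork, visual acuity and questionnaire scores.
- **Remove:** baseline significance tests, and the Greenhouse-Geisser sentence, since two time points leave no sphericity to violate. Report within-arm changes descriptively.

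The cost is analysis wording only. Baseline IOP is already collected, and no procedure or sample size changes. As the Abstract reports data collection complete, the change should be dated and recorded before the masked analysts see allocation.

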### Objectives

This study aims to evaluate changes in IOP after the use of the EyePeace ocular massager. We hypothesize that EyePeace will achieve a more consistent and pronounced IOP reduction compared to digital ocular massage. Furthermore, the observed IOP reduction may be correlated with morphological changes in underlying ocular structures.

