## Methods

### Study Design

This single-masked, randomized controlled trial will enroll 36 healthy Chinese participants (72 eyes) aged 18 years or older. They will be randomly assigned in a 1:1:1 ratio to the digital ocular massage group (24 eyes), EyePeace ocular massage group (24 eyes), or no ocular massage (24 eyes). The trial will be conducted at Tianjin Medical University Eye Hospital (TMUEH) in Tianjin, China, a nationally accredited clinical trial site. Healthy participants who voluntarily consent to undergo ocular massage will be invited to join this study to assess noninvasive clinical parameters. Patients and the public will not be involved in the design, implementation, reporting, or dissemination of this study. This study was registered on the Chinese Clinical Trial Registry (ChiCTR2400093512) on December 6, 2024.

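### Holm's correction is valid here, but with three arms it tests the second-smallest P value at .025 where .05 is permissible, giving away some power on contrasts such as EyePeace versus digital massage

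*Protocol article*

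**What the plan says.** The trial has three arms allocated 1:1:1 (Study Design). The Objectives section names a pairwise hypothesis: "We hypothesize that EyePeace will achieve a more consistent and pronounced IOP reduction compared to digital ocular massage". On testing, Statistical Methods gives "The significance level is set at 5% (2-tailed), with a 95% CI", plans a two-way repeated measures ANOVA, and then says "Multiple comparisons will be made between groups at different time points using the Bonferroni-Holm correction". The two assessments are at baseline and 10 minutes after the intervention (Participant Timeline). The sentence does not give the number of comparisons in the family. It could be three (the arm pairs after the intervention) or six (three pairs at each of two time points).

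The Sample Size section assumes "a common SD of 1.9 and a maximum mean difference in IOP between groups of approximately 2 mmHg" and says the stated numbers "are required to achieve 90% power at α=.05". That power belongs to the overall test: "The calculations use a 1-way analysis of variance to test overall mean differences". No power is given for any single pair, and the position of the middle arm is not stated.

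**The concern.** Holm is a general method that assumes no logical relation among the hypotheses. For three P values in ascending order it uses the limits .05/3, .05/2 and .05. The .05/2 at the second step guards against two equalities still being true after one has been rejected. Among three means this cannot happen: if two pairs are equal, so is the third. The stricter second limit therefore protects against nothing and costs power.

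What is at stake is a contrast that need not give the smallest P value. If digital massage lowers IOP somewhat, EyePeace versus digital is a smaller difference than EyePeace versus no massage, so its P value tends to come later in the order. The loss occurs only when the second P value lies above .025 and at or below .05. Holm then stops, and that contrast is lost. The third contrast is lost with it if its P value is also at or below .05. The third step itself carries no penalty, because Holm also tests it at .05.

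**Working it through.** **Inputs.** From Sample Size: SD 1.9 mm Hg, largest difference 2 mm Hg, 24 eyes per arm, α = .05. From Study Design: three arms, 36 participants, so 36/3 = 12 participants per arm. Assumed: the position of the middle arm, and independence of the analysed units.

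**1. The plan's own figure.** One-way ANOVA with means evenly spaced over 2 mm Hg (deviations -1, 0, +1):

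- f² = [(1 + 0 + 1)/3] / 1.9² = 0.667/3.61 = 0.185
- noncentrality = 72 × 0.185 = 13.3, with 2 and 69 degrees of freedom
- power = 0.902, and 24 is the smallest number per arm that reaches 0.90

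The stated size reproduces with eyes treated as independent. Even spacing is also the least favourable pattern for a fixed range.

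**2. The logic.** Call the three equalities H1, H2 and H3. The intersection of any two is the same as all three together. The closed family therefore holds only the global null and the three single nulls. Testing the global null by Bonferroni (smallest P ≤ .05/3) and then each single null at .05 controls the family-wise error strongly at 5%. This is Shaffer's procedure for three groups.

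| Ordered P | Holm limit | Shaffer limit |
|---|---|---|
| smallest | .0167 | .0167 |
| second | .025 | .05 |
| third | .05 | .05 |

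No Shaffer limit is below Holm's, so every Holm rejection is also a Shaffer rejection. As an invented illustration, P values of .010, .030 and .040 give one rejection under Holm and three under Shaffer.

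**3. Power for EyePeace versus digital.** Simulated with pooled-variance t tests on the follow-up contrasts, SD 1.9. Means are for no massage / digital / EyePeace.

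| Units per arm | Assumed means | Holm | Shaffer |
|---|---|---|---|
| 24 | 0/-1/-2 | 35.0% | 42.6% |
| 24 | 0/-1.5/-2 | 11.5% | 14.5% |
| 24 | 0/0/-2 | 90.3% | 92.8% |
| 12 | 0/-1/-2 | 16% | 21% |
| 12 | 0/0/-2 | 56% | 61% |

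The gain vanishes when both massage arms lie very far from control, because the second P value is then always tiny. In no simulated trial did Holm reject a pair that Shaffer did not.

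**4. Error control.** With no effect in any arm (24 per arm), the chance of any false rejection is 4.3% for both procedures. With one true equality (means 0/0/-2), the chance of falsely rejecting it is 4.2% under Holm and 5.0% under Shaffer.

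**5. Size of the family.** If Holm is run over six comparisons, power for EyePeace versus digital at 24 units per arm falls to about 21% (0/-1/-2) or 83% (0/0/-2).

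**6. An omnibus gate as an alternative.** The between-arm main effect of the planned repeated measures ANOVA averages baseline with follow-up. Randomised arms should not differ at baseline, so a 2 mm Hg difference becomes 1 mm Hg. With an assumed baseline/follow-up correlation of 0.6, the SD of the average is 1.9 × √0.8 = 1.70. The standardised range falls from 2/1.9 = 1.05 to 1/1.70 = 0.59. Using that test as a gate, with each pair then at .05, gives about 25% power for EyePeace versus digital at 0/-1/-2, below Holm's 35%. For correlations from 0.5 to 0.7 the figure stays at 25% to 26%.

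**The case against.** The strongest reply is that the plan states nothing wrong. Holm is a recognised procedure with strong 5% control, and preferring a less familiar refinement is close to taste. That Holm is valid stands in full. The rest does not quite follow: the refinement is never worse and costs no error control, so the choice is not neutral.

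It can also be said that the gain depends on an assumption the plan does not make. This stands. The figure of 7 to 8 points belongs to an evenly spaced middle arm, and the other two placements shown at 24 units per arm give 2.5 to 3 points.

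A third reply is that the size of the family matters more. Also true: at 0/-1/-2, narrowing from six comparisons to three moves power from 21% to 35%, against 35% to 43% for Holm to Shaffer. The .05/3-then-.05 rule is justified only for a family of three, so the family has to be fixed in any case.

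Finally, the Abstract reports data collection as complete. Replacing a published correction with a more liberal one at that stage needs documenting and defending. That stands as a condition on how the change is made.

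**Conclusion.** The point holds as a minor, free improvement. For the three pairwise contrasts of three arms, Holm's second limit is stricter than 5% control requires. Replacing it by Shaffer's raises power for EyePeace versus digital by between 0 and about 8 percentage points, depending on where the middle arm lies. Family-wise error stays at or below 5%.

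A reader might infer more than the document supports:

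- **That the correction is an error, or that the stated power is wrong.** Neither is so. The 90% belongs to the overall ANOVA, reproduces under the plan's assumptions, and is untouched by this point.
- **That the change rescues the hypothesis in the Objectives.** With an evenly spaced middle arm the contrast still has only about 43% power at 24 units per arm and 21% at 12.
- **That any omnibus test followed by unadjusted pairs would serve as well.** Gating on the main effect of the planned ANOVA can lower power below Holm's. Even an F test on follow-up values alone does not dominate Holm in every data set.

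The power figures treat units as independent, as the plan's calculation does for eyes. Correlation between a participant's two eyes lowers all of them but does not reverse the ordering.

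**What to change.** Replace the Holm sentence in Statistical Methods with wording to this effect: *For the primary outcome, the multiplicity family consists of the three between-arm contrasts of post-intervention IOP (or of change in IOP). They are tested by Shaffer's modification of the Holm procedure for three groups: the smallest P value at .05/3 and, if it is rejected, the remaining two at .05 each.*

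Choose post-intervention value or change, and name that one only. Do not offer a gate on the between-arm main effect of the repeated measures ANOVA as an alternative.

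The cost is one or two sentences. No extra participants or measurements are needed, and the procedure can be worked by hand from three P values. Because data collection is reported as complete, the change should be dated and recorded, with its reason, before any unmasked comparison of arms. The Allocation section says the analysis team is masked, which makes this possible if the masking is still intact.

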### Interventions

Eligible participants will be randomly assigned in a 1:1:1 ratio to (1) digital ocular massage (group A), (2) EyePeace ocular massage (group B), or (3) no ocular massage (group C). Group A and group B participants will receive ocular massage for 10 minutes [5,10,11]. Any participant experiencing an adverse event (AE) will be withdrawn from the trial, documented, provided appropriate treatment, and referred immediately to the principal investigator (PI). Clinical research staff will receive professional training covering participant enrollment, treatment procedures (including risks and benefits), and data collection processes. Participants will be sufficiently informed about the study and provided with compliance education to enhance participation and minimize noncompliance. Study staff will proactively contact participants in advance by telephone or SMS text message. EyePeace is a flexible, medical-grade silicone device designed to apply gentle, pulsatile vertical pressure to the closed eyelids. Although it does not contain a built-in pressure gauge, manufacturer specifications suggest that the applied force typically ranges from 0.2 to 0.5 N. To ensure consistency, all participants in the EyePeace ocular massage group received standardized instructions and a demonstration before use. In addition, a trained examiner supervised the massage procedure to ensure correct technique and duration. For the digital ocular massage group, clinical staff applied consistent fingertip pressure guided by prior training and feedback from pilot sessions, aiming to replicate the mechanical effect of the EyePeace ocular massage device. Although exact biomechanical equivalence between digital ocular massage and EyePeace ocular massage cannot be assured, the standardization procedures were designed to ensure comparability in massage duration, eyelid area coverage, and application frequency.

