### Primary Outcome: IOP

The study’s primary outcome is assessing IOP (mm Hg) before and after the intervention. All participants will undergo ophthalmologic examinations on the same day. A slit lamp examination will first be performed on all eyes, followed by IOP measurement in the sitting position, using an iCare IC100 rebound tonometer (iCare Finland Oy) [19]. The instrument will be calibrated regularly according to the manufacturer’s instructions. A disposable, single-use probe was loaded into the device and aligned 4 to 8 mm perpendicular to the central cornea. Six consecutive measurements were performed. The software automatically discarded the highest and lowest values, and the IOP was calculated from the remaining 4 values. Only proper measurements (indicated by a green background within acceptable limits) were included.

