### Classification of AEs

Any unexpected symptoms or signs that may pose a risk to the physical or mental well-being of participants will be classified as AEs. Localized AEs may include intolerable dry eye symptoms, keratitis, severe corneal ulcers, conjunctivitis, eye irritation, and blurred vision. Mild AEs, such as temporary dry eyes or foreign body sensation, which do not affect daily activities, will be managed by suspending the intervention, administering artificial tears, and re-examining participants after 30 minutes. Moderate AEs, such as conjunctivitis or slightly elevated IOP, will be managed by suspending the treatment, referring to the PI, providing targeted treatment, and following up until the symptoms resolve. In the event of a serious AE, the PI and the TMUEH Medical Ethics Review Committee will be promptly notified, the trial will be immediately suspended, and appropriate medical intervention will be provided to ensure participant safety and minimize further risk.

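### The adverse-event summary names only the two massage groups and leaves the groups compared undefined, so the randomised no-massage rate is not promised beside the massage rates

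*Protocol article*

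**What the plan says.** The AE analysis takes two sentences in Statistical Methods. The first sets the scope of the description: "the distribution of AEs will be described for both digital ocular massage and EyePeace ocular massage groups". The second gives the test: "The incidence rates of AEs were compared using the chi-square test or the Fisher exact test, as appropriate". It does not say which groups are compared. Nowhere else does the article commit to describing AEs in the no-massage group.

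Other sections bear on what that group could contribute:

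- Study Design and Interventions randomise participants 1:1:1 to digital massage (A), EyePeace massage (B) or no massage (C).
- Data Collection and Management: "All participants will undergo a comprehensive ophthalmic examination at baseline and after the intervention". Table 1 schedules the assessments at both time points without restriction by group.
- Primary Outcome describes the rebound tonometry, with the probe "aligned 4 to 8 mm perpendicular to the central cornea. Six consecutive measurements were performed".
- Classification of AEs defines an AE without reference to cause or group: "Any unexpected symptoms or signs that may pose a risk to the physical or mental well-being of participants will be classified as AEs". Its examples are broad: "Localized AEs may include intolerable dry eye symptoms, keratitis, severe corneal ulcers, conjunctivitis, eye irritation, and blurred vision".
- Data Collection and Management, on capture: "All AEs are documented and reported to the trial steering committee".

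**The concern.** The main safety question in a trial with an untreated arm is whether the intervention adds harm to what would have happened anyway. Several listed events, such as irritation or blurred vision, can plausibly occur without massage, whether by chance or after repeated eye examinations. The article does not say that the examinations cause them; this is an inference, but it fits a definition of AE that ignores cause. Group C is the means of measuring that background rate, and its events should already be on record.

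If the summary covers only A and B, the reader sees two massage rates with nothing to set them against. If the test is also restricted to A and B, equal rates would look the same whether massage caused every event or none. The Introduction presents EyePeace as lowering the risk of complications and the Discussion calls safety assessment crucial, so the safety table is likely to be read closely.

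**Working it through.** **Step 1. Scope of the text.** Three groups are randomised, examined and covered by AE documentation. Two are named in the AE description. The groups in the test are not named. Because the test sentence directly follows one about A and B, massage versus massage is its most natural reading, but a three-group test is not excluded.

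**Step 2. The plan's own figure.** There is none for AEs; the article says only that they are unlikely. The Sample Size section supplies the denominators: 36 participants / 3 groups = 12 per group, so 2 × 12 = 24 massage participants and 12 controls.

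**Step 3. Background events among massage participants.** Assume the same background rate p per participant in every group. No value of p stands in the document, so a range is used. Expected number in A and B together = 24p; expected number in C = 12p; chance of at least one in A and B = 1 − (1 − p)^24.

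| Assumed p | Expected in A + B (24p) | Expected in C (12p) | Chance of at least one in A + B |
|---|---|---|---|
| 5% | 1.2 | 0.6 | 1 − 0.95^24 = 0.71 |
| 10% | 2.4 | 1.2 | 1 − 0.90^24 = 0.92 |
| 20% | 4.8 | 2.4 | 1 − 0.80^24 = 0.995 |

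So about 1 to 5 massage participants would be listed with an event that massage did not cause, and a two-group summary gives no way to see this.

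**Step 4. A risk that both massages share.** Assume that each massage adds 30 percentage points to the background rate. The probability that a two-sided Fisher exact test gives P ≤ .05 is the sum, over all tables with P ≤ .05, of the product of the two binomial probabilities.

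| Assumed background | Rate in A and in B | A vs B (12 vs 12) | A vs C (12 vs 12) | A + B vs C (24 vs 12) |
|---|---|---|---|---|
| 5% | 35% | 0.02 | 0.26 | 0.41 |
| 10% | 40% | 0.02 | 0.23 | 0.39 |
| 20% | 50% | 0.02 | 0.21 | 0.36 |

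The A versus B column is only the false-positive rate of the test, because A and B do not differ. It would not rise with more participants in any useful way. The comparison with C responds to the excess, although its power is low at this size.

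**The case against.** The strongest reply is that this is an ambiguity in wording and that the control group is not lost. Much of that stands.

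- **The test sentence names no groups.** A reader might infer that the chi-square or Fisher comparison is massage against massage. The text does not say so, and a 3 × 2 table would satisfy it. The same section also says that all participants are analysed as allocated. That general statement does not override the specific sentence limiting the description to A and B.
- **No sentence attributes every event to massage.** A reader might infer that the plan charges all events to massage. It does not. The accurate statement is that, without a control rate alongside, massage effects cannot be separated from other sources.
- **Control data are not discarded.** AEs are documented in all groups. The Quality of Vision Questionnaire and visual acuity are scheduled at baseline and follow-up in all three groups, and 0-10 pain and discomfort scores are added to the questionnaire. Part of the symptom burden therefore has a randomised comparison. This does not replace an AE table, and the questionnaire section is itself worded as before and after massage with paired tests.
- **AEs are expected to be rare and power is poor.** Both are true. At a 5% background rate only 1.2 events are expected in the massage groups and 0.6 in controls. This argues for showing counts and intervals rather than relying on tests; it is no reason to leave one group out.
- **Table layout can wait for an analysis plan.** It can, but the article does not leave the scope open: it states a two-group description.

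**Conclusion.** The point holds in a limited form. The article commits to describing AEs for two of three randomised groups and does not define the comparison. As written, the safety summary carries no concurrent control rate, and the most natural reading of the test cannot detect a risk common to both massages. It would go too far to say that the plan attributes all events to massage, that it definitely tests only A against B, or that it throws the control group away.

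The size depends on assumptions, because the document gives no AE rate: about 1 to 5 of 24 massage participants with an unrelated event at background rates of 5% to 20%. These figures use the planned 36 participants; the Results section reports 50 recruited, so the analysed groups may be somewhat larger. The gain from including group C is mainly descriptive. This is a free improvement and does not threaten the primary analysis.

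**What to change.** Amend the two sentences in Statistical Methods so that they:

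- describe AEs in all three randomised groups, counting each participant once, since most contribute two eyes;
- name the comparisons: each massage group, or pooled massage, versus no massage, alongside digital versus EyePeace;
- report differences in incidence with exact 95% confidence intervals, and label them descriptive because precision is low at about 12 participants per group.

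The cost is an extra column in the AE table and a few intervals. Data collection is reported as complete, but the change affects only the analysis and reporting of events that the article says are already documented. It should be recorded, with its date, before the masked analysis team receives the group codes, or declared as a later clarification if that has already happened.
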